## Abstract

COPD (chronic obstructive pulmonary disease) is a medical condition that encompasses several chronic, progressive, and severe respiratory illnesses, such as emphysema and chronic bronchitis. COPD is the 4th most deadly disease in the world and its prevalence is expected to increase. Despite the abundance of information on the disease's etiology, pathophysiology, and treatment possibilities, it has long been underdiagnosed and underreported for a long time, particularly in developing countries. The symptoms of COPD result in significant impairments and significant impact on quality of life. COPD is the third leading cause of death in Pakistan. According to the published literature, COPD has been found to be associated with a serious economic burden, either the direct cost to healthcare systems in the form of frequent hospital admissions or indirect costs to patients suffering from COPD. Despite the availability of excellent medication, COPD treatment goals are frequently not achieved resulting in poor management of COPD. The recent studies revealed that due to the missing role of Pharmacists in most of the public sector hospitals of Pakistan, the COPD disease management protocols are not being properly followed. Pharmacists can help the healthcare system by implementing these management protocols that focus on patient education about the disease, prescribed medications, and proper inhalation techniques. Furthermore, the pharmacists as an effective healthcare's team member properly educate the patients about the ongoing assessments and their willingness to follow treatment recommendations and quit smoking, while referring them to smoking cessation programs as needed, following the GOLD guidelines. This aim of this clinical trial is to evaluate the impact of implementing standard treatment guidelines and the role of pharmacists in implementing GOLD guidelines for COPD management.

## Introduction

1

The primary manifestation of COPD is restricted airflow in the airways and is most commonly associated with an atypical allergic reaction in the lungs triggered by harmful environmental substances. This condition also leads to decreased lung flexibility or emphysema [1,2]. The current state of is alarming as it affects 2.7 million individuals annually. COPD is predicted to become the third most common disease by 2030, if left untreated or without effective preventive measures [1,3,4]. The literature suggests that COPD's annual mortality rate from COPD could exceed the combined death rates of lung cancer and breast cancer [5,6]. Smoking is the primary underlying factor in COPD, accounting for around 85–90 % of all COPD cases [7]. The quality of life negatively impacted by COPD, which increases healthcare resource utilization and spending. While a lack of proper pharmacotherapy may impair patient and healthcare outcomes, overtreatment should also be avoided. Especially indications for inhaled corticosteroids (ICS) have become fewer, due to their unfavorable cost-benefit-ratio, with regard to serious adverse events and the superior effectiveness of long-acting bronchodilators (BD) in decreasing exacerbations [8]. COPD is becoming a significant global health challenge, with a particular emphasis in developing regions. In addition to the smoking as a risk factor, the lack of disease awareness among the general population and the inadequate implementation of treatment guidelines also play a role in contributing to the prevalence of COPD [9]. To ensure that COPD patients receive adequate care, it is crucial to adhere to standardized treatment protocols. The Global Initiative for Chronic Obstructive Lung Disease (GOLD), established in 2001, plays a pivotal role in enhancing the diagnosis, management, and prevention of COPD, to improve the treatment outcomes for COPD patients. Each year, a new report is generated through an extensive examination of published studies, to enhance the practices of healthcare providers in COPD management. These GOLD reports are widely recognized as crucial, evidence-based reference materials for implementing effective management protocols and represent the current guidelines for the care of individuals with COPD [10]. The GOLD guidelines, which were initially introduced in 2011, were created to provide healthcare providers with the most suitable recommendations for diagnosing and managing COPD patients. This handbook has been revised and updated with the new guidelines in the years including 2006, 2011, 2017 and 2021. The updated handbook with the new indispensable instruments has received noticeable attraction by the clinical practicians across the world [11,12]. Taking into account the significance of COPD guidelines for disease management in many different countries, clinicians treating various patient populations exhibited poor adherence to GOLD guidelines recommendations [[13], [14], [15], [16], [17], [18], [19], [20], [21], [22]], specifically over-treating the patients [20]. The World Health Organization (WHO) states that the factors affecting the adherence of pulmonology specialists to guidelines are highly intricate, encompassing not just the physician but also factors related to the patient, the disease itself, and social aspects [21,23]. Regardless of the obstacles, patients' clinical outcomes are negatively impacted by inadequate adherence which increases the risk of unforeseen acute exacerbations of COPD [24,25]. Enhanced adherence can lead to clinical and functional advantages, as well as economic benefits that reduce both direct and indirect healthcare costs [16,[26], [27], [28], [29]].

As, COPD is the 3rd most prevalent non-communicable disease, there is limited data available on therapeutic and economic outcomes related to COPD in Pakistan [5]. In Pakistan, there is a lack of data on the clinical and economic outcomes of Medicare beneficiaries with COPD who reside in long-term care (LTC) facilities [30]. Despite the benefits of guideline-complying therapy, various cross-sectional studies demonstrated that GOLD-implementation was suboptimal, likely due to physicians’ poor familiarity with guidelines. It is evident that there is a lack of knowledge about clinical realization of recommended therapy settings [31,32].

Pharmacists have the ability to provide education on disease, medication treatment, and healthcare guidelines and policies to either healthcare practitioners or patients. Therefore, they can collaborate with physicians to implement the COPD GOLD guidelines. The aim of this study is to implement the recommendations of the GOLD guidelines in healthcare settings in Pakistan.

### Objectives

1.1

A.**Research Hypothesis:** Integrating the standardized protocols outlined in the GOLD guidelines into clinical practices will enhance COPD management in Pakistan.B.**Study objectives:** The objective of this research is to evaluate the enhancement of COPD management by implementing standardized treatment guidelines, to improve treatment outcomes, slow down disease progression and enhancing the quality of life. This endeavor is expected to have a positive impact by reducing the frequency of acute exacerbations, emergency visits, and hospital stays. Therefore, it will indirectly result in alleviating the healthcare burden of COPD on the healthcare system in Pakistan.

### Trial design

1.2

In order to effectively carry out this ongoing clinical trial, an exploratory randomized controlled study design with three arms is necessary. These arms include Group A (receiving usual therapy), Group B (receiving Pharmaceutical Care, encompassing pharmacological and non-pharmacological treatments in accordance with GOLD guidelines) and Group C (receiving Usual Treatment along with an educational intervention). Patients will be randomly assigned to one of these three arms based on their medical record numbers, with 1:1:1 allocation ratio. The trial was meticulously designed to comply with the Standard Protocol Items: Recommendations for Interventional Trials (SPIRIT), and the checklist of SPIRIT guidelines is included in (Appendix A).

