
### Eligibility criteria

2.2

Patients who meet all the specified inclusion criteria and none of the stated exclusion criteria will be eligible for participation. The enrollment period is scheduled to last 24 weeks for assessing primary outcomes and 48 weeks to assess secondary outcomes.A.**Diagnostic criteria:** The study's focus will be on individuals who experience dyspnea and chronic cough with sputum production as their target population. Clinical assessment, which includes spirometry will however be used to establish the diagnosis. To confirm the persistent airflow limitation, the Forced Expiratory Volume (FEV1)/Forced Vital Capacity (FVC) ratio must be less than 0.70.B.**Inclusion Criteria:** Patients who are eligible to participate in the trial must meet all of the following criteria at the time of randomization: **a)** Patients should exclusively receive care in the Outpatient COPD wards **b)** They must have a confirmed diagnosis of COPD by the hospital consultant, which includes a FEV1/FVC ratio of less than 0.70 compared to the predicted normal value, and a history of two or more acute exacerbations (emergency visits) within the past 6 months to 1 year **c)** A comprehensive diagnosis will be conducted to assess any co-morbidities **d)** Patients deemed suitable for trial entry by the consultant and who possess a clear understanding of the study's significance, demonstrate good compliance with the researcher's observations and evaluations, willingly accept participation in the clinical trial, and complete the clinical consent form, will be included in this study.C.**Exclusion Criteria:** Patients who have mobility issues, confusion, disorientation, terminal illness or congestive heart failure will not be included in the study. Additionally patients who are currently enrolled in any rehabilitation programs or seeking consultation with a clinical pharmacist or pulmonary physiotherapist will be excluded [34,35].

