### Recruitment

2.6

The principal investigator will undertake the recruitment of participants from Holy Family Hospital in Rawalpindi, Pakistan, following the screening, randomization, and follow-up process outlined in Fig. 2 of the CONSORT Flow Diagram. Participants in the trial will be given a brief overview of the trial's objectives, methodologies, potential side effects, and advantages. The following two primary strategies will be implemented to ensure an adequate number of participants during the enrollment phase, which will last for 24 weeks.1.Disseminating recruitment materials in prominent hospital locations, including the outpatient lobby and ward entrances.2.In cases where potential participants are identified within the hospital wards, either the hospital's inpatient staff or the principal investigator will approach them to gauge their interest in participating

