### Methods: assignment of interventions (for controlled trials

2.7

A.**Sequence Generation:** Participants will be assigned randomly to either the control or experimental groups, following a 1:1:1 allocation ratio determined by a computer-generated randomization schedule.B.**Confidentiality:** The personal medical records of the subjects will only be granted access to by the principal investigator of the clinical trial.

The principal investigator will also be required to sign an “Investigator Statement” or “Confidentiality Agreement” affirming their commitment to maintaining confidentiality. Data handling will strictly adhere to a “data anonymization” approach, ensuring that any information that could reveal the specific identity of the subjects is excluded. The allocation sequence will be generated by the principal investigator and the hospital's health care team, participants will be enrolled, and they will be assigned to interventions.

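### Two unreconciled allocation methods are stated, and the principal investigator who recruits also helps generate the sequence, so upcoming assignments can be foreseen

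*Protocol article*

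**What the plan says.** The protocol article describes allocation in two places.

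- Section 1.2, Trial design: "Patients will be randomly assigned to one of these three arms based on their medical record numbers, with 1:1:1 allocation ratio".
- Section 2.7, Sequence Generation: participants are assigned "following a 1:1:1 allocation ratio determined by a computer-generated randomization schedule".

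It also states who does what.

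- Section 2.7: "The allocation sequence will be generated by the principal investigator and the hospital's health care team". The rest of that sentence covers enrolment and assignment and names nobody else.
- Section 2.6, Recruitment: "The principal investigator will undertake the recruitment of participants from Holy Family Hospital in Rawalpindi, Pakistan".
- Section 2.7, Confidentiality: "The personal medical records of the subjects will only be granted access to by the principal investigator of the clinical trial".
- Section 2.2, inclusion criterion (d), rests partly on opinion. It begins "Patients deemed suitable for trial entry by the consultant" and goes on to ask for understanding of the study and good compliance with the researcher.

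On timing, section 2.1 (item C) places random assignment after the consent form is signed, and section 2.8.1 places the baseline assessment before patients enter a group.

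**The concern.** Randomisation protects a comparison only if the person deciding whether a patient enters cannot tell which arm comes next. Two statements in the article put that at risk.

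First, a reader cannot tell which allocation method is in force. If the arm follows from the record number, it is fixed by something already on the chart before the patient is approached. That is quasi-random allocation.

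Second, even if the record-number wording is set aside, the recruiter takes part in making the list.

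At stake is the comparability of the three arms. Section 2.8.2 compares the intervention groups with control, and section 2.3.5 lists three primary outcomes. All of these comparisons rest on the allocation. Regression on baseline variables can reduce measured imbalance but cannot be relied on to remove imbalance in unmeasured prognosis.

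**Working it through.** **Is there a figure to reproduce?** No. The point concerns method and roles, and the article gives no alpha, power, effect size or SD behind its 120 patients. The check is therefore a comparison of sections, followed by an illustration.

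**Step 1: the two methods.** Section 1.2 names the record number as the basis of assignment. Section 2.7 names a computer-generated schedule. They would agree if the record number served only to identify the patient on a random list, but no section says so. Taken at its word, section 1.2 makes the arm a function of a number known before consent.

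**Step 2: the roles.** Section 2.7 makes the principal investigator a co-generator of the sequence, and section 2.6 makes the same person the recruiter. Under section 2.7 alone, the recruiter can know the list. Under the literal section 1.2, the recruiter can also see the number that fixes the arm, since section 2.7 gives this person access to the medical records. Entry requires a history of two or more exacerbations (section 2.2), so the record is likely to be consulted before enrolment.

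**Step 3: room to act.** Criterion (d) in section 2.2 is a judgement, applied with the consultant. Foreknowledge together with a discretionary criterion is what makes selective enrolment possible.

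**Step 4: illustration of size.**

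Inputs:
- 120 patients (section 2.5) at 1:1:1 (section 1.2): 120 / 3 = 40 per arm.
- Assumed: two-sided alpha 0.05, one unadjusted two-arm contrast, normal approximation, no true effect, and a prognostic imbalance of d SD carried fully into the outcome.

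Formulas:
- Standard error of the difference in SD units: sqrt(2/40) = 0.2236.
- Rejection rate: Φ(d/0.2236 − 1.960) + Φ(−d/0.2236 − 1.960).

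| Assumed d (SD) | d/0.2236 | Rejection rate |
|---|---|---|
| 0.1 | 0.447 | 0.073 |
| 0.2 | 0.894 | 0.145 |
| 0.3 | 1.342 | 0.269 |

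To give a sense of scale, suppose 4 of the 40 patients in one arm are steered and differ by 1 SD in prognosis (again an assumption). That arm's mean moves by (4/40) × 1 = 0.10 SD. The same in the opposite direction in a second arm gives a difference of 0.20 SD between them.

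**The case against.** The strongest reply has five parts.

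- **The two descriptions may be compatible.** Both sections speak of random assignment, and record numbers could simply index a computer-generated list. This stands as far as it goes. A reader might infer that the two statements cannot both be true, or that every assignment is knowable in advance under any use of record numbers. The article supports neither: a random list keyed to record numbers is unpredictable to someone who does not hold the list, and no fixed record-number rule is stated. What remains is that the article does not reconcile the two, and that here the recruiter helps make the list.
- **Concealment may be described elsewhere.** A reader might infer that the trial has no concealment. The article condenses a fuller protocol and refers to a SPIRIT checklist in an appendix that is not shown, so its silence proves nothing. The point therefore rests on the stated conflict and the stated roles.
- **Consent and baseline come first.** This is correct (sections 2.1 and 2.8.1). The order governs when the arm is formally given, but not when it can be known.
- **The consultant, not the principal investigator, judges suitability.** This is also correct, and no section says that the consultant knows the sequence. It is only a partial safeguard: the health care team co-generates the sequence, the article does not place the consultant outside that team, and the principal investigator still decides whom to approach.
- **The trial is exploratory, with a feasibility goal** (sections 1.2 and 2.5). This tempers the consequences but does not remove them, because section 2.8.2 still plans between-arm tests.

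**Conclusion.** The point holds in this form: sections 1.2 and 2.7 give two unreconciled allocation methods, the first of which is foreseeable if read literally; and, independently of that, sections 2.6 and 2.7 let the recruiter know upcoming assignments while entry depends partly on judgement. The plan as written thus permits selection bias in every between-arm comparison.

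The size is unknown. The error rates of about 7%, 15% and 27% depend wholly on the assumed shifts of 0.1, 0.2 and 0.3 SD and on the simple contrast described above. They show what modest steering could do in a trial of this size; they do not show that any steering has occurred or is likely.

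**What to change.** 1. In section 1.2, delete the statement that arms are assigned from record numbers, or limit it to identifying the patient.
2. In section 2.7, state the computer-generated schedule as the only method. Have it generated and held by an existing colleague with no part in recruitment, so that neither the principal investigator nor the recruiting team sees it.
3. Release each assignment only after the consent and baseline steps already planned. Sealed envelopes are one way to do this; other means would serve.
4. Section 1.2 calls the trial ongoing, so report the method actually used and how many patients, if any, were allocated by record number. Add a sensitivity analysis without those patients only if enough remain; if most or all were allocated that way, such an analysis would be unworkable and plain reporting is the remedy.

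The cost is a short amendment and a few hours of the colleague's time, assuming that someone outside recruitment is available. No extra patients or study procedures are needed.

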## Methods: participants, interventions, outcomes

2

### Study setting

2.1

A.Selection of the country: Pakistan, being a developing nation with limited resources, faces challenges in adequately addressing a wide range of health issues. In many cases, the management of chronic diseases does not adhere to established treatment protocols, leading to an escalation in healthcare costs.B.**Selection of the disease:** COPD, which ranks as the 3rd leading cause of death in developing countries, including Pakistan, has been reported a major healthcare debacle with high negligence. Hence, we have selected COPD as the focus of our study to assess the response to intervention-based disease management following the standard treatment guidelines.C.**Study design:** Patients recruitment for the trial will be based on strict compliance with both inclusion and exclusion criteria**.** Once they have signed the participant's consent form, they will be randomly assigned to one of three groups: the first group will be the treatment group 1, the second group will be the treatment groups 2, and the third group will serve as the control group. The first treatment group will receive an educational intervention, which will consist of pharmacist counseling that covers information about the disease, medications, and lifestyle modifications. On the other hand, the second treatment group will receive pharmaceutical care, which includes pharmacological interventions and educational interventions in accordance with the GOLD guidelines. The usual care will be provided to the participants in the control groups. The effectiveness of these interventions will be assessed through several measures which include: a) The number of acute exacerbations and hospital emergency visits will be documented based on patients' medical records, including prescriptions and lab reports, throughout the study b) Disease progression will be evaluated using spirometry c) The quality of life of the patients will be assessed using the St. George's Respiratory Questionnaire [33].D.**Description of study settings:** The study will take place within the Medical Outpatient Department (OPD) of Holy Family Hospital, Rawalpindi Medical University in Pakistan, to recruit a total of 120 participants diagnosed with COPD. Following the completion of the clinical trial, the data will be accessible on the trial registry where it was initially registered, as well as on other scientific literature publishing platforms.E.**Informed consent:** Patients will be provided with the informed consent before any study procedures occur.

### Eligibility criteria

2.2

Patients who meet all the specified inclusion criteria and none of the stated exclusion criteria will be eligible for participation. The enrollment period is scheduled to last 24 weeks for assessing primary outcomes and 48 weeks to assess secondary outcomes.A.**Diagnostic criteria:** The study's focus will be on individuals who experience dyspnea and chronic cough with sputum production as their target population. Clinical assessment, which includes spirometry will however be used to establish the diagnosis. To confirm the persistent airflow limitation, the Forced Expiratory Volume (FEV1)/Forced Vital Capacity (FVC) ratio must be less than 0.70.B.**Inclusion Criteria:** Patients who are eligible to participate in the trial must meet all of the following criteria at the time of randomization: **a)** Patients should exclusively receive care in the Outpatient COPD wards **b)** They must have a confirmed diagnosis of COPD by the hospital consultant, which includes a FEV1/FVC ratio of less than 0.70 compared to the predicted normal value, and a history of two or more acute exacerbations (emergency visits) within the past 6 months to 1 year **c)** A comprehensive diagnosis will be conducted to assess any co-morbidities **d)** Patients deemed suitable for trial entry by the consultant and who possess a clear understanding of the study's significance, demonstrate good compliance with the researcher's observations and evaluations, willingly accept participation in the clinical trial, and complete the clinical consent form, will be included in this study.C.**Exclusion Criteria:** Patients who have mobility issues, confusion, disorientation, terminal illness or congestive heart failure will not be included in the study. Additionally patients who are currently enrolled in any rehabilitation programs or seeking consultation with a clinical pharmacist or pulmonary physiotherapist will be excluded [34,35].

